### 3.3.4. Intervention allocation

We will randomize eligible subjects to intervention and control groups at a ratio of 1:2. Randomization will be stratified on three variables, namely depression severity at baseline (BDI2=<19 vs >=20), absolute presenteeism prior to baseline (6 or higher vs 5 or lower, based on the obtained median of the eligible subjects in the pilot run) and center (Office X, Factory Y, Factory Z). Assuming that subjects are recruited from 3 sites, there will be a total of 12 strata. The study statistician will prepare 12 lists of random assignments ahead of time, one for each of the 12 strata. Each list will be blocked to ensure that the ratio of intervention to control is exactly 1:2 at set intervals within each stratum. The statistician will send these lists to the research assistant who is not involved in any other aspects of the study and who will build a spreadsheet that enables concealed sequential allocation and will be responsible for keeping these lists in the safe place.

Before randomizing an individual, the CRC will make a final determination of whether or not the person is eligible to be in the randomized trial. For example, prior to randomization, we will exclude those who score too low (BDI2=<9), which may well occur because of the difference between K6 and BDI2 and due to time elapsed for screening, because those who score too low at baseline will have less room for improvement. Once the CRC determines the eligibility of the participant, she will enter his/her registration number and the stratification variables to the spreadsheet which will automatically generate the allocation according to the pre-determined random sequence. The entered variables cannot be undone in order to guarantee allocation concealment.

Those randomized to control group will be put on a waiting list and after 15 months can receive the telephone CBT if they wish to do so.

One stratification factor is BDI2>=20 and BDI2<=19. This cutoff was chosen because our previous study suggests the score ranges 14-19 to be mildly ill, 20-28 to be moderately ill and 29- to be severely ill (Hiroe et al., 2005) and because our pilot study suggested that this is about the median BDI2 value for employees with K6>=9.

Another stratification factor is presenteeism, because this will be one of our primary outcomes and it is important to make sure that some effect can be seen, when in fact there is, probably among the more disturbed people.

# 4. INTERVENTIONS

## 4.1. Description and schedule

In order for the randomization and start of intervention to be as close as possible, CRC will endeavor to randomize the client the day after the 2^nd^ IC is returned, arrange the 1^st^ appointment and send out the appropriate manuals on the same day.

The telephone counseling makes use of a client manual and a client workbook. We have also prepared a counselor manual. All of these have been modeled after “Creating a Balance: A Step-by-Step Approach to Managing Stress and Lifting Your Mood” (Simon et al., 2006) which has been trialed in two large RCTs and found effective in alleviating major depression when combined with pharmacotherapy in the primary care (Simon et al., 2004) and in the workplace (Wang et al., 2007).

The telephone CBT consists of 8 sessions; 1 for introduction, 3 for BA, 3 for CR and 1 for summary. The contents of the program have been modified and adapted, based on the expert opinions of the PIs of this study and on the feedbacks received from clients in the pilot runs in order to make them more suitable for subthreshold depression among workers in the Japanese culture. For each session, the client has to make a preparation, receive a telephone counseling session for approximately 30-45 minutes, and subsequently do some homework.

The EAP program is the one which has already been in use by this company since 1997. The program includes a web site for mental and physical health, a p.r.n. telephone or in-person counseling service accessible to all the employees and on-site lectures on mental and physical health for managers and workers. For the year 2007, the average service provided per employee was 0.09 mental health self-check-ups on the web, 0.003 telephone counseling session, and 0.001 in-person counseling session. The company paid $3 per person per annum for this much service. In addition, Office X and Factory Y have part-time psychologists who administered 0.13 session per employee in 2006. We will not tell the providers of the EAP program about this telephone CBT trial, but at the same time we will not ask the participants to refrain from telling the EAP personnel about the trial if and when they do contact them.

## 4.2. Quality control of treatments

Maintaining quality of the intervention is very important to maximize the power of the study.

The three supervisors are qualified in cognitive therapy.

The three supervisors and the 9 telephone counselors have received two-day workshop with [name], who developed the original telephone CBT program used in this project or another workshop modeled after the original one.

The psychologists (MSc, PhD and post-PhD levels) have had one individually supervised and two group-supervised cases before acting as counselors in the trial. The supervisors and the counselors will have regular conferences every two months.

All the sessions will be audiotaped. The adherence of the session contents will be checked by the counselor self-checklist, which will further be checked by the CRC on an on-going basis. A random 10% subset of the audiotaped sessions, from early/middle/late phases of the study, will be assessed by the supervisors using the same checklist, and reported back and discussed at the regular counselors’ meetings. The degree of adherence by an independent rater and the degree of concordance between the self-check and an independent assessor’s rating will be reported.

## 4.3. Measures of client adherence

The CRC will check for client adherence and notify the therapist and his/her supervisor if any of the following is noticed:

1. More than 3 weeks have elapsed since the allocation
2. More than 3 weeks have elapsed between sessions
3. K6 >=10 for any of the sessions at session #2 or afterwards
4. K6 >=6 for any of the sessions at session #5 or afterwards

# 5. ASSESSMENTS

## 5.1. Measures

### Beck Depression Inventory-II (BDI2)

The Beck Depression Inventory, originally published in 1961 (Beck et al., 1961), has been the most widely used self-report measure of depression severity. With the advent of the DSM-IV, the time frame and question items have been updated as the 2^nd^ edition of the BDI, and its reliability and validity have been confirmed (Beck et al., 1996). The reliability and validity of the Japanese version have been found to be excellent (Hiroe et al., 2005).

We will administer BDI2 at baseline, at 4-month follow-up (end of acute phase treatment) and at 15-month follow-up.

### Health and Productivity Questionnaire (HPQ)

The World Health Organization health and Productivity Questionnaire (HPQ) is a self-report instrument designed to estimate the workplace costs of health problems in terms of self-reported sickness absence (absenteeism) and reduced job performance (presenteeism). Validation studies have found documented significant associations (r=0.61 to 0.87) of HPQ work hours assessments with payroll records (Kessler et al., 2003a) and job performance assessments with supervisor ratings (r=0.52) (Kessler et al., 2004) and other administrative records (area under the curve, 0.58 to 0.72) (Kessler and Ustun, 2004).

We will administer HPQ at screening, at 4-month follow-up (end of acute phase treatment) and at 15-month follow-up.

### K6

K6 is a recently developed very short (6-item) self-report questionnaire to screen for common mental disorders (Kessler et al., 2002). It is based on modern item response theory methods and consists of questions that are maximally discriminative of respondents in the 90^th^-99^th^ percentile range of the general population distribution because it is known that between 5-10% of the population suffer from mental disorders at any point in time. Only items displaying constant psychometric characteristics across sociodemographic variation are included in the final model. K6 has been found to work as well as and better than some widely used screening questionnaires (Furukawa et al., 2003; Kessler et al., 2003b). The Japanese version has been validated (Furukawa et al., in press).

We will use K6 as the initial screening instrument. In addition, we will use K6 as a process measure in the course of the telephone CBT and administer it at the beginning of every session. Together with the screening, 4-month follow-up and 15-month follow-up data (which will all be administered to the control group as well), K6 will be one of the secondary outcome measures.

### Composite International Diagnostic Interview (CIDI)

The CIDI is a widely used fully-structured diagnostic interview for assessing mental disorders, to be used with the general population by trained lay interviewers (Robins et al., 1988). It has been successively updated to accommodate the DSM-IV. We used the most recent computerized version (Kessler and Ustun, 2004) and administered the sections for mood disorders and alcohol use. The concordance between the CIDI and standardized clinical assessments has been reported (Haro et al., 2006). The Japanese version of the HPQ and CIDI has been used in the World Mental Health Survey in Japan (Kawakami et al., 2005). [[name], could you supplement? Is there any validation study?]

## 5.2. Follow-up visit description and schedule

### 5.2.1. Drop out from the intervention

The subject is free to withdraw from the intervention and/or the study at any time. However, we plan to make sure that the therapists and the CRC know how important it is to ask those who drop out of the intervention to complete the 4-month follow-up. Even if someone discontinues participation in the intervention, we will therefore make every effort to collect outcome data from them at the follow-ups at month 4 and at month 15.

If a new mental condition arises or the existing mental condition worsens, all the participants, whether during the telephone CBT or outside of the CBT, are free to utilize the EAP routinely made available by the company and/or seek professional help outside the company. In addition, they can call up the free hotline connected to the study center psychologist. If a new mental condition or worsening of the existing subthreshold depression occurs during the telephone CBT such that treatment outside the current program is advisable, the counselor must advise the subject to seek professional in-person help from the industrial physician, his/her home doctor or a mental health specialist. The participation in the intervention itself can be continued if the counselor and the subject see no conflict between the telephone CBT and the newly offered treatment, or discontinued should there be any perceived conflict or wish to withdraw expressed from the part of the subject. Even if the telephone CBT itself is discontinued, the subject is encouraged to take part in the 4- and 15-months follow-ups.

### 5.2.2. Drop out from the study

Those who withdraw consent to the follow-ups at 4 and/or 15 months will be considered dropouts from the study.

### 5.2.3. How to enhance adherence and reduce dropouts

Dropout from the intervention will be strictly distinguished and differentiated from dropout from the study. We will ask the client, so far as it is possible with him/her, that he/she respond to the final assessment even if he/she has chosen to stop the telephone counseling itself.

The explanation for IC will emphasize the client’s susceptibility/vulnerability based on the screening data and potential benefit from the program, in order to enhance his/her adherence.

A brochure (e.g. page 208, page 212 of the textbook) may help.

Taking IC twice will likely eliminate those half-hearted volunteers and/or also enhance adherence among the more determined.

We will send out New Year Cards to both the intervention and the control groups for the year 2010, which is right before the 15-month follow-up for the first cohort, and in 2011. We will send out a thank-you card after 4-month and 15-month follow-ups. It will be very good if we can give any reward, monetary or otherwise, especially to those people who respond to the 4-month [this is our primary outcome] and 15-month follow-up, but this needs to be negotiated with the sponsor.

## 5.3. Assessment of response variables

### 5.3.2. Independence of the self-reports

Our primary outcome, the BDI2 to be completed by the participant, is mailed back confidentially to the CRC and not to the therapist, in order to assure anonymity and independence of the ratings.

It is explicitly explained in the letter that these data will not be shared with the counselor, so honest disclosure is most welcome.

### 5.3.1. Data collection

#### 4-month follow-up (Acute-phase outcomes)

In the intervention group, the primary outcome will be measured at 4 months post randomization, i.e. approximately one month after the last session of the telephone counseling.

In the control group, the endpoint assessment will take place at 4 months post randomization.

The questionnaires will be mailed to the participants. If no response is received within 2 weeks, a second set of questionnaires with an appropriate cover letter will be mailed. If no response is still available, CRC will call the participants, both in the active treatment or control groups. Telephone response to the questionnaire battery is accepted.

#### 15-month follow-up

Both the intervention group and the control group will receive questionnaires at 15 months post randomization.

The CRC will first send out a notification postcard two weeks before actually sending out the questionnaires. Then the questionnaires will be mailed to the participants. If no response is received within 2 weeks, a second set of questionnaires with an appropriate cover letter will be mailed. If no response is still unavailable, CRC will call the participants, both in the active treatment or control groups.

### 5.3.3. Training of CIDI interviewers

CIDI will be administered by two interviewers with extensive prior training and experiences, and three interviewers who will have been trained and will have done a dozen pilot interviews.

All the other response variables are self-reports.

### 5.3.4. Quality control of assessments

Ongoing:

The CRC will check all the self-reports and get back to the participants should there be any missing data. The CRC will monitor the progress of all the therapy sessions and follow-ups according to the predefined criteria.

Periodic:

Cf. DSMC.

Post hoc:

All the CIDI interviews, both at baseline and at 15-month follow-up, will be audiotaped and a random 10% subset will be monitored for inter-rater reliability. The CIDI raters will not be blind to the treatment allocation for logistic reasons, because the CRC is responsible for approximately half of the CIDI interviews.

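### The allocation-aware coordinator telephones late month-4 responders, and her share of the CIDIs is the reason given for leaving all raters unblinded; existing staff and varying blocks could reduce both exposures cheaply

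*Protocol*

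**What the plan says.** **Who knows the arm.** Under Protocol 3.3.4, "Before randomizing an individual, the CRC will make a final determination of whether or not the person is eligible", and then "she will enter his/her registration number and the stratification variables to the spreadsheet which will automatically generate the allocation". Under 4.1 the CRC randomises, books the first session and sends the manuals. Under 4.2, 4.3 and 5.3.4 she checks session checklists, watches client adherence and monitors therapy progress. She therefore knows every allocation.

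**CIDI rating.** Protocol 5.3.4 states: "The CIDI raters will not be blind to the treatment allocation for logistic reasons". The reason follows in the same sentence: "the CRC is responsible for approximately half of the CIDI interviews". Section 5.3.3 says: "CIDI will be administered by two interviewers with extensive prior training and experiences, and three interviewers who will have been trained". Section 3.3 names two people for the screening CIDIs.

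**Month-4 outcomes.** Under 5.3.1, questionnaires are mailed twice. The CRC then calls those who have not replied, in both arms, and "Telephone response to the questionnaire battery is accepted". Under 5.3.4 she also goes back to participants about missing items. Under 5.3.2 the BDI2 is returned to the CRC and kept from the therapist.

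**Allocation lists.** Section 3.3.4 says "there will be a total of 12 strata" and "Each list will be blocked to ensure that the ratio of intervention to control is exactly 1:2 at set intervals within each stratum". An otherwise uninvolved research assistant keeps the lists, and spreadsheet entries are irreversible. No block size is given. Nothing says that the size varies or is withheld from the CRC.

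**The concern.** In an open-label trial with self-reported primary outcomes, the biases worth removing are those that staff can introduce and that better task assignment avoids. Here three tasks meet in one person who knows the arms: the last eligibility decision, some of the late primary outcome collection, and a large share of the only interviewer-rated measure.

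The justification for unblinded CIDI rating does not reach as far as the decision. It explains why the CRC cannot be blind, not why the other interviewers should know the arm.

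The consequences differ in weight. Month-4 telephone collection bears on the BDI2 and HPQ, which decide whether the intervention worked. The 15-month CIDI bears on time to a depressive episode, a secondary outcome. The blocking bears on who is entered, and when.

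**Working it through.** **1. The plan's own figures.** For 1:2 allocation, d = 0.40, two-sided alpha 0.05 and 90% power (3.2):

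- n(active) = (1 + 1/2) × (1.960 + 1.282)² / 0.40² = 1.5 × 10.51 / 0.16 = 98.5, so 99, with 198 controls and 297 in total. This reproduces the plan.
- With 90% response, 89 and 178 remain (267). SE of the difference = √(1/89 + 1/178) = 0.130 SD. Power for d = 0.42 is 89.9%, against the stated 90%.

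Nothing below changes the sample size.

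**2. Which CIDIs are exposed.** Section 5.3.4 places CIDIs at baseline and at 15 months. By 3.3.1 and 3.3.4 the baseline CIDI precedes randomisation, so its rater cannot know the arm. Only the 15-month CIDI is open to rater knowledge. It is the natural source for time to incident episode (2.2), although the protocol does not state that link outright.

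**3. Month-4 telephone collection.** The protocol does not predict the share of answers given by telephone. The ranges here are assumptions: share f = 10% to 30% in both arms, and an arm-dependent bias b = 0.2 to 0.5 SD among those answers. The shift in the group difference is f × b. The false-positive risk is the two-sided rejection rate under no true effect, with SE 0.130.

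| f (of 267) | b (SD) | shift (SD) | two-sided false-positive risk per outcome |
|---|---|---|---|
| 10% (27) | 0.2 | 0.02 | 3.5% + 1.7% = 5.3% (from unrounded tails) |
| 20% (53) | 0.5 | 0.10 | 11.7% + 0.3% = 12.0% |
| 30% (80) | 0.5 | 0.15 | 21.1% + 0.1% = 21.1% (from unrounded tails) |

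The result runs from negligible to material, and the document does not say where the trial would fall.

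**4. Predictability of allocations.** Suppose the block size is constant and known. An allocation is then certain beforehand when all remaining places in the block belong to one arm. With a CBT and c control places, the expected number of certain-control places is c/(a + 1), and of certain-CBT places a/(c + 1).

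| Block (assumed) | certain control | certain CBT | total / block size | certain CBT / block size |
|---|---|---|---|---|
| 3 (1+2) | 2/2 = 1.000 | 1/3 = 0.333 | 1.333/3 = 44% | 11% |
| 6 (2+4) | 4/3 = 1.333 | 2/5 = 0.400 | 1.733/6 = 29% | 7% |
| 9 (3+6) | 6/4 = 1.500 | 3/7 = 0.429 | 1.929/9 = 21% | 5% |

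Full enumeration of the blocks gives the same values. With equal strata there would be 297/12 = about 25 people in each, so a constant block of 3 would repeat about eight times and could be noticed.

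**5. Workload of moving the 15-month CIDIs.** If the CRC would otherwise do half of 297 with no attrition, 148.5 interviews move. That is 16.5 a month over 9 months or 12.4 over 12. Shared among four others (assuming the CRC is one of the five), it is about 4.1 or 3.1 extra a month each.

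**The case against.** **Allocation.** A reader might infer that the CRC will know up to 44% of allocations, or that enrolment passes through someone who already knows the arm. The document supports neither. It does not say that block size is constant or that the CRC is told it, and she would have to track 12 strata. The arm appears only after an irreversible entry, and the lists are held elsewhere. Most of the certain positions would be control. Eligibility rests mainly on K6, BDI2 and CIDI results, with exclusion 8 in 3.1.2 the main matter of judgement, and the CRC aims to randomise the day after consent returns. Omitting block size from a protocol is ordinary and helps concealment. What stands is that custody and irreversible entry prevent tampering, not deduction from allocations already seen.

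**Independence of self-reports.** A reader might infer that CRC calls break the promise in 5.3.2. They do not: that section promises independence from the therapist and names the CRC as recipient.

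**Telephone collection.** Calls follow two mailings, apply to both arms and limit missing primary data. The items are fixed, and participants know their arm anyway. That the CRC records the answers herself is the natural reading, but it is not spelled out. What stands is that an avoidable extra route for bias reaches the primary outcomes.

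**CIDI.** The instrument is fully structured (5.1), interviews are audiotaped, and a random 10% are checked for inter-rater reliability. The lack of blinding is disclosed. The CRC's half is a share of all CIDIs, so a reader should not take it as a stated share of those at 15 months. What stands is the gap between a reason specific to the CRC and a decision that covers every rater.

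**Feasibility.** Sections 3.3 and 5.3.3 give different numbers of interviewers, so availability at 15 months is not established.

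**Conclusion.** The point holds as a cheap improvement, not as evidence that the design is unsound. The protocol gives the allocation-aware CRC the month-4 calls, and uses her share of the CIDIs to justify leaving every rater unblinded although other interviewers are planned.

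The telephone route matters most because it reaches the primary outcomes. The 5.3% to 21% range rests wholly on assumed shares and biases and is no forecast. It would be wrong to conclude that the primary result will be biased by a known amount. The CIDI part is limited to a secondary outcome in exploratory analyses. Concealment is weakened rather than absent, and the predictability percentages apply only to a constant block size that the CRC knows or infers.

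**What to change.** 1. Generate the lists with randomly varying block sizes (for example 3, 6 and 9), known only to the statistician and the list holder. The cost is regenerating 12 lists.
2. Assign the 15-month CIDIs to already planned interviewers other than the CRC, without access to allocation, and have them record any unblinding. The CRC can keep doing baseline CIDIs. First confirm which interviewers in 5.3.3 are available and reconcile that number with 3.3.
3. Have the same interviewers, not the CRC, complete month-4 questionnaires by telephone. Record mode of collection (mail or telephone) and run a sensitivity analysis of the primary outcomes on mode.

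Sample size is unchanged and no new posts are needed if those interviewers are available. The main cost is rescheduling up to about 149 interviews. Participants may still reveal their arm, so this removes routine staff knowledge of allocation from these tasks but cannot guarantee blind assessment.
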